## Abstract

**Background:**

Family caregivers are confronted with high demands creating a need for professional support and at the same time hindering its utilization. Telephone support allows easier access than face-to-face support because there is no need to leave the person with dementia alone or find an alternative carer. It is also independent of transport possibilities or mobility. The objectives are to evaluate whether telephone-based cognitive-behavioral therapy, which is implemented in established care provision structures, improves outcomes compared to usual care and whether it is as effective as face-to-face cognitive-behavioral therapy.

**Methods/Design:**

If participants live in the area of one of the study centers (Jena, Berlin, Munich) and indicate that attendance of a face-to-face therapy is possible, they will be assigned to the face-to-face group. The other participants will be randomized to receive either telephone-based cognitive-behavioral therapy or usual care. Data will be collected at baseline, post-intervention, and at a 6-month follow-up. The primary outcomes will be depressiveness, burden of care, health complaints, and problem-solving ability. The secondary outcomes will be anxiety, quality of life, violence in caregiving, utilization of professional assistance, and cost effectiveness.

**Discussion:**

This paper describes the evaluation design of our telephone-based cognitive-behavioral therapy in a randomized controlled trial. If this intervention proves to be an effective tool to improve outcomes, it will be made accessible to the public and the use of this support service will be recommended.

**Trial registration:**

German Clinical Trials Register DRKS00006355.

## Background

Numerous studies have shown that family caregivers, particularly those who care for a relative with dementia, face extremely burdensome demands and life changes, which impacts their health and quality of life. Increased morbidity [1] and mortality rates [2] and higher prevalence rates of anxiety and depressive disorders [3] are reported. These consequences are well documented and indicate a strong need for adequate professional support.

For family caregivers, accessing professional support is often difficult and existing support services are used insufficiently. Caregivers often need to monitor the person with dementia for most of the day. Especially elderly caregivers may themselves suffer from decreased mobility. Additionally, a large proportion of this group lives in rural areas where personal support services can be hard to reach. Therefore, the challenges family caregivers face create a special need for professional support and, at the same time, can hinder its utilization.

A possible solution is telephone-based support. It allows easier access than face-to-face support because there is no need to leave the person with dementia alone or find an alternative carer. It is also independent of transport possibilities or mobility. A telephone-based short-term intervention for family caregivers of people with dementia (Tele.TAnDem: a cognitive-behavioral telephone-based intervention for family caregivers of people with dementia that can also be delivered face-to-face) was already tested for feasibility, efficacy, and acceptability in a previous study [4].

In the present study, Tele.TAnDem will be implemented in established care provision structures (Alzheimer Society) for the first time. The aim of our study is to assess the effectiveness of this integrated intervention in a randomized controlled trial. The primary objective is to evaluate whether telephone-based cognitive-behavioral therapy (TEL) improves depressiveness, burden of care, health complaints, and problem-solving ability compared to usual care. The secondary objectives are to evaluate whether (1) TEL is as effective as face-to-face cognitive-behavioral therapy (F2F), (2) a two-day training program (8h) in Tele.TAnDem for behavioral therapists is sufficient to achieve an adequate and effective implementation of the intervention, (3) the TEL intervention is a cost-effective or possibly even cost-saving alternative compared to usual care, and (4) TEL increases the use of professional support by family caregivers of people with dementia compared to the control group.

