### Sample size

Based on results of meta-analyses [1,17,18], we can expect interventions for caregiving relatives of people with dementia to have small to medium effects on the mental and physical health of caregivers (*d*=0.14 to 0.41). Results from the previous project [4] similarly indicate that this telephone-based intervention has small to medium effects (*f*=0.18 to 0.29).

Hypothesizing a small effect size in a two-group design with three measurement points, an *α* of.05, a power (1−*β*) of.80, and a *ρ* of.50, we need a sample of *n*=82 per group [19]. Therefore, we aim to have 164 participants in the randomized groups. Assuming a dropout rate of 30%, we plan to recruit 118 persons in each randomized group. Additionally, we aim to recruit as many people for the F2F group as possible (with *n*=118 as cut-off criterion).

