### Data analysis

The data will be analyzed with SPSS version 22.0 (IBM Corp., Armonk, NY) and MPlus version 7.0 (Muthén & Muthén, Los Angeles, CA). Data cleaning and analyses will be performed using SPSS/Mplus syntax operations. Possible baseline differences between trial arms will be statistically tested and further analyses will be adjusted for imbalances in the baseline scores. The primary analysis will be by intention to treat. For the primary outcomes, analyses will be corrected for multiple testing.

As sensitivity analyses, completers of all assessments will be analyzed separately. Hypotheses tests will be performed at *α*=.05. The numeric outcomes will be analyzed using analyses of variance; categorical outcomes will be analyzed using *χ*^2^-tests. Additionally, latent change model analyses will be performed for continuous longitudinal outcome data. To handle missing data, full information maximum likelihood estimation will be conducted in MPlus. As part of the questionnaire adaptation, factor, reliability, and correlation analyses will be performed.

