## Discussion

This study will evaluate whether TEL improves depressiveness, burden of care, health complaints, and problem-solving ability compared to usual care and assess whether TEL is as effective as F2F. One strength of this study is its robust design and follow-up assessment allowing evaluation of the long-term effects of TEL. For the first time, it will be possible to test intervention effects of TEL in established care services.

However, there will also be several challenges in this study. In particular, enrolling a sufficiently large sample in the F2F group will be a major difficulty, which we hope to overcome by recruiting via different media and by directly assigning participants to F2F.

The F2F sample will be especially selective, as it will consist of an exclusively urban and mobile population. Since possible F2F participants will be selected from the overall recruited sample, the remaining subsample being randomized will potentially be more rural and less mobile than the original sample recruited.

To ensure adequate and homogeneous application of therapeutic strategies, extensive training prior to implementation, application through CBT-qualified therapists, regular supervision (4 to 6 times per year) and documentation of the implementation will be essential strategies. To determine treatment integrity, independent CBT-qualified therapists will assess psychotherapeutic competence and adherence in randomly selected audio and video recordings of the sessions.

In case the intervention is terminated prematurely, an attempt will be made to continuously include the participant in the data collection. To avoid selective dropout in the control group, this group will receive an incentive. Blinding is not possible in the design of the proposed study, since both the family caregivers and the therapists will know whether a therapy is conducted. To nevertheless guarantee an independent assessment of intervention efficacy, the data collection will be performed by researchers who are not involved in the therapy.

In summary, this will be the first study to test the implementation of telephone-based cognitive-behavioral therapy in established care provision structures in a randomized controlled trial. If TEL proves to be effective in improving primary outcomes, our results will be relevant to practice. Hence, TEL could be used on a large scale. Thus, the results of the study will be used to improve support services for family-caregivers.

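### Secondary objective (1) asks whether TEL is as effective as F2F, but the protocol names only difference tests and sets no minimum F2F size, so the named analysis cannot support that conclusion

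*Protocol article*

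**What the plan says.** The comparison with face-to-face therapy is posed three times in the protocol article, always as a question of equal effectiveness. The abstract asks "whether it is as effective as face-to-face cognitive-behavioral therapy". Secondary objective (1) in the Background asks whether "TEL is as effective as face-to-face cognitive-behavioral therapy (F2F". The opening of the Discussion says the study will "assess whether TEL is as effective as F2F".

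The Data analysis section describes inference once, for all outcomes and comparisons. "Hypotheses tests will be performed at" α = .05, "The numeric outcomes will be analyzed using analyses of variance", categorical outcomes get χ² tests, and "latent change model analyses will be performed for continuous longitudinal outcome data". Nothing there separates the F2F comparison from the comparison with usual care.

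The sample size is derived for the randomized groups only: "Hypothesizing a small effect size in a two-group design with three measurement points", giving 82 per group and 118 recruited after 30% dropout. For the other group, "we aim to recruit as many people for the F2F group as possible", with 118 as the cut-off. The Design section makes F2F a non-randomized group. The Discussion expects F2F enrolment to be a major difficulty and describes the group as urban, mobile and especially selective.

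**The concern.** A test of difference can show that two treatments differ. It cannot show that they are alike, because failure to reject may reflect either similarity or imprecision. A claim of equal effectiveness needs a stated largest acceptable deficit and an interval that excludes it. Here the objective is of the second kind and the named tests are all of the first kind.

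The F2F sample size makes this worse. It has a ceiling but no floor, and recruitment is expected to be hard. Under a difference test, fewer F2F participants mean a wider standard error and a higher chance of finding no significant difference. If that finding were taken as the answer to objective (1), weaker data would favour the conclusion. At stake is how the TEL versus F2F result can be interpreted. The evidence that TEL works against usual care is not in question.

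**Working it through.** **1. The protocol's own sample size.** Inputs from the Sample size section: two groups, three measurements, α = .05, power .80, ρ = .50, a small effect (taken as f = 0.10, since no value is given). For the group-by-time interaction in a repeated-measures ANOVA, λ = N·m·f²/(1−ρ) with df = 2 and 2(N−2).

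- N = 164: λ = 164 × 3 × 0.01 / 0.50 = 9.84, power 0.805.
- N = 162: λ = 9.72, power 0.7998, just short.
- So 164 in total, 82 per group, and 82/0.70 = 117.1, rounded up to 118.

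The stated figures reproduce exactly. They are a calculation for detecting a difference between TEL and usual care, and they say nothing about TEL versus F2F.

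**2. What a difference test would do for TEL versus F2F.** Assumptions, not document figures: outcome SD = 1, one time point, two-sided .05, normal approximation. F2F is taken to reach its cut-off with the same 30% dropout (118 × 0.70 = 82.6, so 82). Baseline adjustment at r = .50 leaves a variance factor of 1 − 0.50² = 0.75. An F2F group of 40 is included to show poor recruitment, and 118 versus 118 as the best case with no dropout.

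SE = √(v(1/n₁ + 1/n₂)), with v = 0.75 adjusted or 1 unadjusted. For 82 versus 82, adjusted: √(0.75 × 2/82) = 0.135.

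P(non-significant | deficit δ) ≈ Φ(1.96 − δ/SE). At δ = 0.2: Φ(1.96 − 1.479) = Φ(0.481), about 68%. At δ = 0.3: Φ(1.96 − 2.218) = Φ(−0.258), about 40%.

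Non-inferiority margin reachable at 80% power, one-sided .025, with no true difference: (1.96 + 0.84) × SE = 2.80 × 0.135 = 0.38.

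| TEL vs F2F analysed | Baseline adjustment | SE | Non-significant at 0.2 SD | Non-significant at 0.3 SD | Margin at 80% power |
|---|---|---|---|---|---|
| 82 vs 82 | r = .50 | 0.135 | 68% | 40% | 0.38 |
| 82 vs 82 | none | 0.156 | 75% | 52% | 0.44 |
| 82 vs 40 | r = .50 | 0.167 | 78% | 57% | 0.47 |
| 82 vs 40 | none | 0.193 | 82% | 66% | 0.54 |
| 118 vs 118 | r = .50 | 0.113 | 57% | 24% | 0.32 |

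**3. What a proper test would do with the same numbers.** For 82 versus 82, adjusted, and a margin of 0.2 SD (assumed), non-inferiority power is Φ(0.2/0.135 − 1.96), about 32%. Two one-sided 5% tests at ±0.2 SD have essentially no power, because the 90% interval half-width is 1.645 × 0.135 = 0.22, which already exceeds the margin.

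**4. Scale.** The Sample size section expects caregiver interventions to achieve d = 0.14 to 0.41. A reachable margin of 0.38 SD is 0.38/0.41 = 93% of the upper end and exceeds the lower end. With that margin, non-inferiority could be declared while TEL had lost most of the benefit expected of such interventions.

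**The case against.** The strongest reply is that the Data analysis section is generic, never mentions TEL versus F2F, and comes from a condensed article. A margin for a secondary comparison could properly sit in the full protocol or analysis plan. That stands as far as it goes: the absence of a margin is not in itself the fault. What remains is that the article does state its tests and its α, and these do not fit an objective it states three times. It also addresses F2F size directly and gives no lower bound. A later plan could add a margin, but it could not by itself supply the sample.

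Four stronger readings are tempting, and the document does not support them.

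- **That p > .05 will be declared equivalence.** No sentence says so. It is an inference from pairing the objective with the only tests named.
- **That wide roll-out hangs on this comparison.** The abstract and the Discussion tie the recommendation to TEL improving outcomes, which the Background makes the primary objective against usual care.
- **That a relevant deficit would usually be missed.** In the main scenario that holds at 0.2 SD (68%) but not at 0.3 SD (40%), and at 0.41 SD only about 14% would be missed. The document does not say which deficit matters.
- **That the F2F group will be small.** Its cut-off equals the TEL recruitment target. The problem is the missing floor, and even the best case of 118 versus 118 reaches a margin of only 0.32 SD.

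It can also be said that an interval and a margin would not rescue a non-randomized comparison. That is right. As the Design section describes it, people who live near a centre and can attend go to F2F, so TEL and F2F barely overlap on the characteristics that assigned them. Confounding could hide a difference or create one, and adjustment for other variables can remove only part of it.

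**Conclusion.** The concern holds as a mismatch between one secondary objective and the analysis named for it. Followed as written, the difference tests cannot support a conclusion that TEL is as effective as F2F, and lower F2F recruitment would make a non-significant result more likely.

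The percentages rest on assumptions: 82 evaluable F2F participants, a single time point and r = .50 for baseline adjustment. That adjustment favours the plan, because the Data analysis section commits only to adjusting for baseline imbalances. Across the scenarios shown, the reachable margin runs from 0.32 to 0.54 SD, so the conclusion does not depend on the exact choice.

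The randomized comparison with usual care, its sample size and the recommendation tied to it are untouched. The point is worth correcting, but the trial does not stand or fall on it.

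**What to change.** For objective (1), replace the difference test with the estimated TEL minus F2F difference and its 95% confidence interval. Adjust for the baseline score and, because F2F is non-randomized, for the collected caregiver and care-situation characteristics that differ between the groups. State that equal effectiveness will not be concluded from p > .05, but only if the interval excludes a margin that is pre-specified and justified for each outcome on which the claim would rest.

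If no defensible margin is reachable at the expected F2F numbers, or if confounding by location and mobility is judged to remain after adjustment, reword the objective to estimating the difference between TEL and F2F. Given the figures above, rewording is the more realistic course.

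The cost is the wording of one secondary objective and its analysis, with no change to recruitment, treatment or the primary analysis. The price is that the trial probably cannot claim equivalence with face-to-face therapy.

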## Methods/Design

### Design

This study is a non-blinded two-armed parallel randomized controlled trial with a third non-randomized group. Participants will be asked whether they reside in the area of a study center and can participate in the F2F. If this is the case, they will be assigned to the F2F group. If this is not the case, they will be randomly assigned to the TEL group or usual care. Random allocation will be on a 1:1 ratio basis but separated for gender and will take place after the baseline assessment. All participants will receive information materials on care and dementia. Assessments will be conducted at baseline (T0), post intervention (T1) and a 6-month follow-up (T2) (Figure 1). The TEL group will receive 12 psychotherapy sessions on the phone, whereas the F2F group will receive 12 psychotherapy sessions in direct contact in one of the participating treatment centers.

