### Procedure

Once potential participants contact the study center, they will be screened for meeting the eligibility criteria in a manual-based telephone interview. Additionally, information on the participants’ sex as well as the possibility of taking part in F2F will be assessed in this screening.

After a positive screening, all potential study participants will receive an information package including information about the study, informed consent forms for study participation and data processing as well as for telephone contact, information for the person with dementia, and several leaflets on dementia and caregiving.

For the first assessment, participants will be contacted by phone, an appointment for the telephone interview will be made for about two weeks later, and the questionnaires will be sent out. This survey technique is used because a mostly elderly study population is expected. In addition, the acceptance of the survey is to be improved and the risk of missing data or dropout to be reduced. In the telephone interview, comprehension difficulties and unanswered questions will be discussed and the questionnaires will be reviewed for completeness. After the telephone interview, the questionnaires will be returned in a return envelope.

Participants will be allocated to the three study groups after finishing the baseline assessment (T0). To ensure a sufficient number of caregivers taking part in F2F, all participants living in Berlin, Jena or Munich for whom attendance is possible will be allocated to the F2F intervention, as long as their mobility is given. A bias is not expected because the participants will not be aware of being exclusively allocated to F2F, as they will be informed about being randomized to one of the three groups. The random number generator Random.org will be used for randomization. After being informed about their group allocation, participants in the intervention groups will receive the therapy sessions. After 6 months, when the therapy is finished, the T1 assessment will be conducted. After another 6 months, the T2 assessment will be conducted. The control group will receive an allowance for participation of 40 EUR, which will be transferred after completion of the study.

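### Randomization is separated for gender, but no stated TEL versus usual-care analysis includes gender: a small, conservative loss of precision is possible and costs almost nothing to avoid

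*Protocol article*

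**What the plan says.** Under Design, the protocol article describes allocation to TEL or usual care: "Random allocation will be on a 1:1 ratio basis but separated for gender and will take place after the baseline assessment". Under Procedure, sex is recorded at the screening interview, and the method is given as: "The random number generator Random.org will be used for randomization". Neither section says whether allocation is blocked within gender.

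Under Data analysis, the methods are named by family. For numeric outcomes: "The numeric outcomes will be analyzed using analyses of variance". Categorical outcomes get χ² tests. In addition, "latent change model analyses will be performed for continuous longitudinal outcome data". Baseline differences between arms are to be tested, after which "further analyses will be adjusted for imbalances in the baseline scores". Gender is not mentioned in that section.

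**The concern.** A factor that defines the randomization strata normally belongs in the analysis. If the arms are balanced on gender by design, gender cannot contribute to the arm difference. A model without gender nevertheless leaves its variance in the residual, so the reported standard error exceeds the true sampling variability and the test is conservative.

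The stated covariate rule does not repair this. It concerns scores, which gender is not. Even on a broad reading it is triggered by imbalance, which stratification is there to prevent. The one factor built into the allocation is therefore among the least likely to enter the model.

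What is at stake is precision. The trial is sized for a small effect at 80% power and will correct its primary outcomes for multiple testing, so it has little precision to spare.

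**Working it through.** **1. The plan's own sample size.** Sample size gives the inputs: "Hypothesizing a small effect size in a two-group design with three measurement points", α = .05, power .80, ρ = .50, and 82 per group (N = 164). The small effect has no number; f = 0.10 is assumed here.

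- Group-by-time test: λ = f²·N·m/(1−ρ) = 0.01 × 164 × 3 / 0.5 = 9.84, with 2 and 324 degrees of freedom. Power is 0.805, and 164 is the smallest even N that reaches .80.
- Between-group test, with f = 0.18 (the lower figure from the previous project): λ = f²·N·m/(1+(m−1)ρ) = 0.0324 × 164 × 3 / 2 = 7.97, with 1 and 162 degrees of freedom. Power is 0.801, and again N = 164.
- Dropout: 82/0.7 = 117.1, so 118 per group.

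The stated figures reproduce. They do so under two different tests, so the sample size does not settle which contrast is meant. That matters in step 4.

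**2. How much variance gender might explain.** The document gives neither the gender share nor a gender effect, so both are assumed. With p the share of men and d the gender difference in within-gender SD units, R² = p(1−p)d² / (1 + p(1−p)d²):

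- p = .20, d = 0.3: 0.0144/1.0144 = 0.014
- p = .25, d = 0.5: 0.0469/1.0469 = 0.045
- p = .30, d = 0.7: 0.1029/1.1029 = 0.093

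A range of 0 to 0.10 covers these.

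**3. Post-score comparison, allocation balanced within gender.** The unadjusted standard error is too large by the factor k = 1/√(1−R²). Type I error is 2[1 − Φ(1.96k)]. Power, against .80 with gender in the model, is Φ(1.96 + 0.84 − 1.96k).

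| R² | k | Type I error | Power |
|---|---|---|---|
| 0 | 1.000 | 0.050 | 0.800 |
| 0.01 | 1.005 | 0.049 | 0.797 |
| 0.02 | 1.010 | 0.048 | 0.794 |
| 0.04 | 1.021 | 0.046 | 0.788 |
| 0.06 | 1.031 | 0.043 | 0.782 |
| 0.10 | 1.054 | 0.039 | 0.769 |

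These figures are for a numeric outcome. An unstratified χ² test errs in the same direction; its size was not computed.

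**4. Dependence on the model and on blocking.** A simulation used n = 164, 80% in one gender (assumed), within-person correlation .50 given gender, a gender effect constant over time, and 4,000 repetitions. Mean model standard errors at R² = 0.10:

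| Analysis | Blocked, without gender | Blocked, with gender | Unblocked, without gender | Unblocked, with gender |
|---|---|---|---|---|
| Post score | 0.156 | 0.148 | 0.156 | 0.149 |
| Change score | 0.148 | 0.148 | 0.148 | 0.149 |
| Post score adjusted for baseline | 0.131 | 0.129 | 0.131 | 0.129 |

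- Blocked post score: 0.1559/0.1478 = 1.055, in line with the formula's 1.054.
- Change score: no difference under blocking, because a constant gender effect cancels. The same holds for a group-by-time test; only a gender-by-time effect would remain.
- Baseline-adjusted: 0.1307/0.1286 = 1.016, because the baseline score already carries most of the gender effect.
- Unblocked post score: the unadjusted model SE (0.1563) matches the empirical SD of the estimate (0.1565), so it is correctly sized. Adding gender still lowers the empirical SD to 0.1493.

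**The case against.** The strongest objection is that this rests on silence. Data analysis is a two-paragraph summary in a journal article. It names model families without listing factors, an analysis of variance can contain gender, and nothing excludes it. Covariate lists are commonly left to an analysis plan, and none is shown. Much of this stands: the document does not say that baseline scores are the only adjustment, and gender may be named elsewhere. But the article goes beyond silence. It states its own rule for choosing adjustments, and that rule is ill-suited to a stratification factor.

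The second objection is that the mechanism needs balance within gender, which is not stated. This stands in full. Separate randomization by gender does not by itself force balance, and with simple randomization in each stratum the unadjusted standard error is right. The lack of a statement does not show that blocking is absent either, so the effect must be put conditionally.

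The third objection is that three measurement points and latent change models point to tests from which a constant gender effect cancels. This stands for those tests. Data analysis does not confine itself to them, however: the analyses of variance are unspecified, the latent change models are additional, and χ² tests are planned.

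A reader might also infer that the standard errors are certainly too large, that the p-values are invalid, or that the benefit of stratifying is lost. The documents support none of these. Blocking and the prognostic strength of gender are not given, and any error is conservative. Whatever arm balance the allocation achieves is kept whichever model is fitted; only some reported precision is forgone.

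**Conclusion.** The point holds as a minor one. Allocation is separated for gender, no stated analysis includes gender, and the stated adjustment rule is unlikely to add it. If allocation is balanced within gender and gender is prognostic, between-arm post-score or categorical comparisons may be somewhat conservative. At the assumed upper limit of R² = 0.10, a post-score standard error is about 5% too wide, type I error is about 0.039, and the power loss is about 3 points (0.800 to 0.769). At R² = 0 there is no effect. Once the baseline score is in the model, the excess at that upper limit is under 2%. For change-score and group-by-time tests it is nil unless the gender effect varies over time. Without blocking, the standard error is correctly sized, and the case for including gender rests on handling chance imbalance and gaining precision. The R² range is an assumption, because the document gives neither the gender share nor a gender effect.

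**What to change.** Add one sentence to Data analysis, for example: *Gender, the randomization stratum, is a prespecified factor in every TEL versus usual-care model, regardless of observed imbalance: a factor in the analyses of variance, a covariate in the latent change models, and a stratification or adjustment variable in the tests of categorical outcomes.* If an analysis plan already says this, a cross-reference is enough.

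The cost is one degree of freedom per model. Sex is already recorded at screening, so no new data are needed. If gender turns out to be irrelevant, the price is negligible: in the unblocked simulation at R² = 0, the post-score standard error rose from 0.1565 to 0.1570, about 0.3%. The 82 per group, 164 in total and 118 per group to be recruited do not change.
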